## Abstract

**Introduction:**

Fibromyalgia causes long-term pain. It affects at least 2% of the population, the majority being women. In addition, extended symptoms corresponding to vitamin B_12_ deficiency occur. Findings from several studies have indicated that vitamin B_12_ may be a possible treatment for pain in fibromyalgia. The aim of the proposed study is to evaluate whether vitamin B_12_ decreases pain sensitivity and the experience of pain (ie, hyperalgesia and allodynia) in women with fibromyalgia.

**Methods and analysis:**

The study is a randomised, placebo-controlled, single-blind, clinical trial with two parallel groups which are administered mecobalamin (vitamin B_12_) or placebo over 12 weeks. 40 Swedish women aged 20–70 years with an earlier recorded diagnosis of fibromyalgia are randomised into the placebo group or the treatment group, each consisting of 20 participants. Outcomes consist of questionnaires measured at baseline and after 12 weeks of treatment. A final re-evaluation will then follow 12 weeks after treatment ends. The primary outcome is tolerance time, maximised to 3 min, which is assessed using the cold pressor test. In order to broaden the understanding of the lived experience of participants, qualitative interviews will be conducted using a phenomenological approach on a lifeworld theoretical basis (reflective lifeworld research approach).

**Ethics and dissemination:**

The protocol for the study is approved by the local ethical committee at Linkoping (EPM; 2018/294–31, appendices 2019–00347 and 2020–04482). The principles of the Helsinki Declaration are followed regarding oral and written consent to participate, confidentiality and the possibility to withdraw participation from the study at any time. The results will primarily be communicated through peer-reviewed journals and conferences.

**Trial registration number:**

NCT05008042.

Strengths and limitations of this studyThe study design is a randomised, placebo-controlled, single-blind clinical trial using parallel groups.The trial is a collaboration between different universities and regions.A possible limitation is the low number of participants; however, the study continues until 20 participants per group have been included and completed the study, which exceeds the minimum number of 16 determined in our power calculation.Another possible limitation is heterogeneity of the fibromyalgia spectrum.Another possible limitation is the placebo effects of parenteral injection; however, the participants are individually randomised to the intervention or the control group (placebo) in a 1:1 allocation ratio.

## Introduction

Fibromyalgia causes long-term pain and affects at least 2% of the population, with 80% of the sufferers being women.^1^ Treatment options are scarce and patients with fibromyalgia have experienced being discredited and invalidated by the healthcare system.^2^ Fibromyalgia is characterised by long-term, widespread musculoskeletal pain and generalised hyperalgesia. This is often accompanied by fatigue, concentration problems and sleep problems.^3^

Fibromyalgia pain is currently classified as nociplastic, which means that pain arises from altered regulation of pain signals, in absence of tissue damage.^4^ No definite pathophysiology has been established for fibromyalgia. Imaging techniques have challenged previous ideas about the peripheral origin of FM and have provided evidence for altered central nervous system nociceptive/pain processing and morphology in fibromyalgia. Furthermore, recent studies report both central alterations and peripheral alterations (eg, systemic low-grade inflammation and nociceptor/muscle alterations).^5–9^

Current treatment for fibromyalgia includes both non-pharmacological and pharmacological interventions, depending on the key symptoms and the extent of disability. The recommended pharmacological treatments for fibromyalgia are antidepressants (eg, Serotonin and norepinephrine reuptake inhibitors (SNRI)) and antiepileptics (eg, gabapentinoids), which often cause side effects.^4^ In addition, opioid analgetics and NSAID (Non-Steroidal Anti-Inflammatory Drugs)/COX (Cyclooxygenase inhibitor) are often prescribed.^10^ Only a minority of individuals report a clinically relevant improvement from any of the treatments.^11^

Vitamin B_12_ is sometimes used for symptoms other than those of vitamin B_12_ deficiency, for example, different pain conditions such as backpain and neuropathic pain.^12–16^ Vitamin B_12_ nasal drops have been tested with positive results on patients with myalgic encephalomyelitis (ME)/chronic fatigue (CF)/fibromyalgia (ME/CF syndrome).^17^ A recent study showed that sublingual vitamin B_12_ had positive effect on patients with fibromyalgia.^18^

In addition, there are vitamin B_12_ studies that have shown good results in the therapy of aphthous ulcers^19^ and acute lumbago,^20^ as well as in studies concerning diabetic polyneuropathy.^21 22^ Moreover, studies examining methylcobalamin treatment in patients with lower back pain showed pain reduction and functionality gain.^13 23^

To summarise, it is not entirely clear how vitamin B_12_ affects the human pain system. However, studies indicate that it may be a possible treatment in fibromyalgia.

### Aims and objectives

The aims of this study are to evaluate the effect of mecobalamin (vitamin B_12_) and to describe lived experiences of pain, health, suffering and well-being in women with diagnosed fibromyalgia.

The primary objective is to evaluate whether mecobalamin (vitamin B_12_), given as an intramuscular injection once a week for 12 weeks compared with placebo reduces pain sensitivity, that is, tolerance time (cold pressor test).

The secondary objective is to evaluate whether intramuscular mecobalamin (vitamin B_12_) compared with placebo reduces pain intensity and pressure pain threshold (Numerical Rating Scale (NRS) and pressure algometry), and increases activity level (questionnaire), quality of life (questionnaire) and perceived effect of a given drug (questionnaire). Furthermore, the ratings of expected effects of a given drug (NRS), the desire for pain relief (NRS) and estimated pain variability (NRS) are evaluated. Qualitative interviews that describe how women with fibromyalgia experience pain, health, suffering and well-being (interviews) will be conducted.

## Methods and analysis

### Study design

The study is an academic randomised, placebo-controlled, single-blind clinical trial using parallel groups. Participants are individually randomised to intervention or control group (placebo) in a 1:1 allocation. In order to broaden and deepen the understanding of the lived experience, an interview will be conducted applying a phenomenological approach on a lifeworld theoretical basis, reflective lifeworld research (RLR) approach.^24^

### Study setting and sample

Swedish women aged 20–70 years with an earlier recorded diagnosed fibromyalgia. Detailed eligibility criteria are presented in table 1.

**Table 1 T1:** Inclusion and exclusion criteria

Inclusion criteria	Exclusion criteria
Diagnosis of fibromyalgia. Women aged 20–70 years. Swedish-speaking. Safe method of contraception. Cobalamin value >250 pmol/L < 800 pmol/L. Kidney function value (relatively) GFR >60 .mL/min/1.73 m^2^. Liver function value. P-ALP 0.6–2.85 µkat/L. P-ALAT 0.15–1.13 µkat/L. Heart function value. Troponin-T <15 ng/L. NT-pro-BNP. <60 years <125 ng/L. NT-pro-BNP. 60 years <300. Given consent to participate.	Previous treatment with B_12_. Known hypersensitivity to the active substance. mecobalamin or an additive. Neuroleptic treatment. Reynaud’s phenomenon. Known neuropathy. Vegan as veganism can lead to B_12_ deficiency. Known heart, kidney or liver disease. Breast feeding. Planned or ongoing pregnancy.

The participants are recruited via advertising in the local newspaper, Facebook, YouTube, Fibromyalgia Association, posters at Linnaeus University, hospitals and healthcare centres. The prospective participant contacts the trial manager via telephone or email and receives oral information. Written information and consent forms (online supplemental file 1) are sent to the participant, who contacts the trial manager for an appointment.

10.1136/bmjopen-2022-066987.supp1Supplementary data

### Intervention and placebo

The active substance of vitamin B_12_ given in the study is 2 mL mecobalamin (5 mg/ml), administered intramuscularly.^25^ Placebo substance is 2 mL sodium chloride (9 mg/ml), isotonic solution for parenteral use (Baxter) intramuscularly.^26^ All participants are informed that their urine may turn red, which may occur during mecobalamin injections.

### Measurements

At the first measurement opportunity, the trial manager and coexaminer 1 carefully follow inclusion and exclusion criteria. Oral information is given again, and consent is signed by the participant and by coexaminer 1. First, the participant answers two questionnaires (short-form McGill Pain Questionnaire (MPQ)^27^ and RAND-36 (RAND-36 Health-Related Quality of Life)),^28^ then stimulation tests (cold pressor test and pressure algometry)^29–33^ are performed followed by pain rating (NRS)^34^ immediately after 1 min and after 3 min. Finally, blood samples for cobalamin (vitamin B_12_), kidney, liver and heart markers are taken. The participant provides an information card about the study’s design, purpose, treatment options and contacts with telephone numbers. The participant is asked about her interest in an interview in connection with the final measurement opportunity. Coexaminer 2 assesses the blood samples and approves the final inclusion. If tests deviate from accepted reference values, the participant is excluded and encouraged to seek medical attention.

After the approved inclusion, an independent chief examiner performs the randomisation. The participant then receives intramuscular injections of the active substance or placebo, once a week for 12 weeks, given by a registered nurse. Before each injection, the participant answers questions in which he or she estimate his or her expected effects of a given drug, desire for pain relief and average pain intensity during the past week (NRS). The participant has the opportunity to postpone the visit for ±3 days, for example, in case of illness or travelling and may miss a maximum of two injections in order to follow per-protocol analysis. Even if the participant is not compliant with the study protocol, the participant may retain the treatment regime for the duration of the study and may be analysed in the main intention-to-treat analysis.

The second measurement takes place after 12 weeks of intervention and three questionnaires (MPQ, RAND-36 and Patient Global Impression of Change (PGIC))^35^ are filled out. The stimulation tests cold pressor test and pressure algometry are performed as well as blood sampling of cobalamin/p (vitamin B_12_). In cases of low cobalamin/p, the participant is encouraged to seek medical attention but is still included in the study.

At the third measurement, which takes place 12 weeks after the end of the intervention, the participant fills in questionnaires (MPQ, RAND-36 and PGIC), undergoes stimulation tests (cold pressor test and pressure algometry), blood sampling of cobalamin/p (vitamin B_12_) together with an interview. If cobalamin/p on this occasion shows that the participant has a low cobalamin value, the participant is encouraged to seek medical attention. For the individual participant, the study ends after 6 months. An overview of the study flow is presented in figure 1.

**Figure 1 F1:**
[figure not shown]
Flowchart of participants, outcome measures and follow-up points. MPQ, McGill Pain Questionnaire; PGIC, Patient Global Impression of Change.

### Outcomes

The primary outcome is tolerance time, maximised to 3 min, which is tested using the cold pressor test.

The secondary outcomes are

Pain experience measured by a pressure algometry test performed on the shoulder, hip, knee and elbow.Possible pain change measured by a pressure algometry test performed on the shoulder, hip, knee and elbow.Subjective experience of pain measured using NRS of 0–10, where 0 is the best outcome.Possible pain change measured using NRS of 0–10, where 0 is the best outcome.Ratings of expectation, desire for relief, using NRS of 0–10, where 0 is the best outcome.Ratings of expectation, pain variability, using NRS of 0–10, where 0 is the best outcome.Activity levels are assessed using MPQ Short Version score of 0–45.Quality of life is assessed using questionnaire RAND-36 score of 0–100.Experience of the effect of the drug, assessed using questionnaire PGIC score of 1–7.Control of vitamin B_12_ is done by measuring cobalamin in plasma.Qualitative in-depth interviews will be conducted to capture women’s lived experiences of pain, health, suffering and well-being.

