#### Short-form MPQ

In this study short-form MPQ of 15 questions^27^ is used, which distinguishes between the sensory–discriminatory and the affective and emotional aspects of the pain experience. Participants are asked to estimate their pain intensity and to describe their pain in predetermined words. They fill in the MPQ on all three measurement occasions.

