#### RAND-36

RAND-36 is a quality-of-life instrument^28^ that aims to measure health-related quality of life, that is, physical, mental and social well-being, not just the absence of illness. The estimation instrument consists of 36 questions of various kinds, for example, on general health, activity, physical health, emotional problems and pain. RAND-36 is filled in by the participant on all three measurement occasions.

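### The activity-level objective is assigned to the short-form McGill Pain Questionnaire, which the protocol describes only as a pain measure, so it cannot be answered as mapped

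*Protocol article*

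**What the plan says.** All references are to the protocol article.

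- **Aims and objectives, activity.** The secondary objective is that mecobalamin lowers pain measures "and increases activity level (questionnaire), quality of life (questionnaire) and perceived effect of a given drug (questionnaire"). The questionnaire for activity is not named here.
- **Outcomes.** The questionnaire is named: "Activity levels are assessed using MPQ Short Version score", with a range of 0–45. RAND-36 (0–100) is listed for quality of life only. The Numerical Rating Scale items state that 0 is the best value; the MPQ line gives a range and no direction.
- **Short-form MPQ.** The instrument has 15 questions and separates the sensory side of pain from "the affective and emotional aspects of the pain experience". Participants rate how intense their pain is and choose from set words to describe it.
- **RAND-36.** Its 36 questions are of various kinds, "for example, on general health, activity, physical health, emotional problems and pain".
- **Aims and objectives, algometry.** The objective is that mecobalamin "reduces pain intensity and pressure pain threshold".
- **Abstract, Introduction.** The aim is to find out whether vitamin B12 "decreases pain sensitivity and the experience of pain".

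**The concern.** The objective names one construct (activity) and the outcome list attaches an instrument that the same article describes as measuring another (pain). If the outcome list is followed literally, a conclusion about activity will be drawn from a pain score. If the team notices the mismatch only at analysis, it will have to choose an activity measure after the data exist, and that choice would no longer be prespecified. The direction is also open: the objective asks for an increase, and the MPQ line does not say whether a higher score is better or worse.

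The same section on aims words the algometry objective as a fall in the pressure pain threshold, although the trial hopes for less sensitivity. The stake there is smaller: the stated hypothesis and the reading of the result, not the analysis.

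**Working it through.** **1. The plan's own figure.** The Sample size section gives 16 per group for a 20 s difference with an SD of 20 s, two-sided 5% and 80% power:

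n = 2 × (1.960 + 0.842)² × (20/20)² = 2 × 7.85 = 15.7, so 16 per group.

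The figure reproduces by the normal approximation. The noncentral t gives 16.7, so 17; with the planned 20 per group its power is 86.9%. This calculation concerns cold pressor tolerance time alone. The article gives no sample size or power for the secondary objectives, so nothing below alters a number.

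**2. Activity level: the sections side by side.**

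| Section | Construct | Instrument |
|---|---|---|
| Aims and objectives | activity, to increase | a questionnaire, unnamed |
| Outcomes | activity | short-form MPQ, 0–45 |
| Short-form MPQ | pain intensity; sensory and affective pain | short-form MPQ, 15 questions |
| RAND-36 | health-related quality of life; activity among the example topics | RAND-36 |
| Outcomes | quality of life | RAND-36, 0–100 |

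The first two rows agree with each other, but the third does not support the second. The fourth shows that an instrument with activity content is in the trial, and the fifth shows that it is not used for the activity objective.

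The range gives a small cross-check. The maximum of 45 over 15 questions is 45/15 = 3 points per question. If all questions carry equal weight (an assumption; the article does not give the scoring), the 0–45 score is the sum over the 15 questions that the article describes as pain questions. That leaves no separate activity component.

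**3. Are the data available?** The Measurements section and the two instrument sections place both the MPQ and RAND-36 at baseline, at 12 weeks and 12 weeks after treatment ends. Remapping therefore needs no new collection.

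**4. Algometry direction.** The section on the pressure algometry test gives the unit as kilopascal and says that pressure is stopped when the participant expresses pain. A lower reading therefore means pain at less pressure, that is, more sensitivity. The aim of less sensitivity corresponds to a higher threshold, so the verb in the objective points the wrong way.

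Does this alter the analysis? Let D be the mean threshold on mecobalamin minus the mean on placebo, in kPa. Statistical methods compares thresholds by t-test and ANOVA, in the same manner as the primary variable, and states no directional rule. D and the size of its t statistic are the same whichever verb the objective uses. Only the sentence that interprets D depends on it.

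**5. Primary objective.** The aims section equates reduced pain sensitivity with tolerance time without saying that the time should lengthen. The section on the cold pressor test records the seconds that the hand stays in the water, so benefit is a longer time. This is the same kind of loose wording.

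**The case against.** The best defence is that the MPQ line is a labelling slip in a condensed article. Statistical methods analyses the MPQ by name with a Mann-Whitney test, and its own section presents it as a pain questionnaire, so the result will exist and an informed reader will take it as pain. The instrument description is also short: the supported statement is that it describes no activity content, not that the questionnaire can be shown from the article to have none.

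Much of this stands, and it limits the harm, but it does not remove the mismatch. The mapping is stated, not left out, and the full protocol could not make both the mapping and the instrument description right.

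A reader might infer four stronger things that the article does not support:

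- **That two secondary objectives cannot be answered.** Algometry is the right instrument for its construct, its outcome lines carry no direction, and its analysis has no directional rule. That objective remains answerable; only its wording is wrong.
- **That worsening would be counted as success.** The aims section sets no success criterion, and the Abstract gives the intended direction.
- **That no MPQ pain result would be reported.** The planned Mann-Whitney analysis of the MPQ contradicts this. What is missing is its listing as a pain outcome.
- **That a particular RAND-36 scale with a known direction is the evident replacement.** The article gives activity only as an example topic and names neither a scale nor its scoring direction.

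**Conclusion.** The point holds for one secondary objective. The outcome list assigns activity level to an instrument that the article describes only as a measure of pain, and as mapped it cannot show whether activity increased. The algometry verb and the loose primary-objective phrase are minor wording errors. The algometry analysis is unaffected, and no sample size, alpha or power figure changes.

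Assumptions: the article's short account of the MPQ is taken as a fair description of its content. That a higher MPQ score means more pain is the natural reading of that account but is not stated; the conclusion does not depend on it. Two-sided testing is stated only for the sample size of the primary outcome; that algometry is tested the same way is inferred from its being analysed similarly.

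**What to change.** Before the data are analysed:

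1. In Outcomes, map activity level to the RAND-36 activity items. The sponsor should name the items or scale and state which direction is better.
2. In Outcomes, list the short-form MPQ score (0–45) as a pain outcome and state its direction.
3. In Aims and objectives, name the activity questionnaire so that it agrees with Outcomes.
4. As minor wording corrections in Aims and objectives, state the algometry objective as an increase in pressure pain threshold, and the primary objective as a longer tolerance time in the cold pressor test.

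The cost is a few lines of text, with the same change carried into the full protocol and any analysis plan. No visit, questionnaire or participant is added. The Mann-Whitney tests planned for MPQ and RAND-36 can stay, applied to the RAND-36 activity score once it is defined.

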#### Cold pressor test

The cold pressor test^29–31^ is measured in number of seconds the participant leaves her hand in the low-temperature water of 5°. Evaluation variables from the cold pressor test become pain threshold (when it starts to hurt) and tolerance time, that is, how long the participant endures the pain. The participants end the test by raising their hands when they can no longer stand it or when the set end time of 3 min has elapsed.

#### Pressure algometry test

The pressure algometry test^32 33^ generates a mechanical pressure against specific points on the body: trapezius (shoulder), epicondyle (elbow), gluteal (outside the gluteal muscles) and medial knee (inside of the knee), which are all accepted in the diagnosis of fibromyalgia. Pressure algometry tests are measured in kilopascal. The trial manager interrupts the mechanical pressure when the participant expresses pain.

#### Numerical Rating Scale

The participants rate their pain intensity on NRS^34^ in connection with the cold pressor test when the participant takes her hand from the water, after 1 min and finally after 3 min. The participants estimate their pain intensity on a scale (NRS) from 0 to 10, where 0 corresponds to no pain at all and 10 corresponds to the worst possible pain. Pain rating is measured in the same way after the pressure algometry test.

The influence of expectation, desire for pain relief and pain variability will be measured before each injection using the same NRS as used for pain ratings. Ratings of expected pain levels will be obtained by asking patients ‘What level of pain do you expect when this treatment starts to have an effect?’ The NRS scale is anchored at the left by the descriptors ‘no pain sensation’ and at the right by ‘the most intense pain sensation imaginable’. Ratings of desired pain relief will be obtained by asking patients ‘How strong is your desire for pain relief?’ The question will be anchored by the descriptors ‘0=no desire for pain relief’ and ‘10=the most intense desire for pain relief imaginable’. Ratings of pain variability will be obtained by asking the participants their average pain intensity that week. These scales have been validated and used in previous studies.^36–40^

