### Statistical methods

The primary endpoint is tolerance time at cold pressor test and will be calculated on the difference between the two groups after 12 weeks and analysed by analysis of variance (ANOVA). Pain thresholds measured by pressure algometry test (Somedic) will be analysed using t-test and ANOVA, similar to the primary variable. Questionnaires (MPQ, RAND-36 and PGIC) will be analysed using Mann-Whitney tests. In cases of minor loss (less than 10%), a mixed model can be used as an alternative to t-test and ANOVA with repeated measurement. For variables with more than 10% loss, imputation of data will be used. Drop-out participants will be described in a specific analysis. Rejection analysis will be performed on the participants who interrupt the study prematurely.

Results will be reported for both intention-to-treat and per-protocol analyses. Intention-to-treat is defined as the participant is placed in the treatment group he or she had been randomised to. Per-protocol is defined as the participant is placed in the treatment group she de facto received and carried out without significant protocol deviations. The per-protocol results will be presented as sensitivity analyses. The participant may miss a maximum of two injections.

Self-reported ratings of desired and expected treatment outcome pretreatment and post treatment will be implemented in linear regression models to predict any of the outcome measures. Repeated ratings of desired treatment outcome, expected treatment outcome and pain variability will be calculated as each participant’s SD from the repeated ratings and implemented in a linear regression model to predict possible outcome measures.

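### Expectation and desire ratings made after treatment has begun are used as predictors of outcome, and the expectation item carries current pain, so an association cannot be read as an effect of expectation

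*Protocol article*

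**What the plan says.** Four sections of the protocol article bear on this point.

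- **Aims and objectives.** Within the secondary objective, "the ratings of expected effects of a given drug (NRS), the desire for pain relief (NRS) and estimated pain variability (NRS) are evaluated".
- **Measurements.** At each injection visit, before the injection, participants "estimate his or her expected effects of a given drug, desire for pain relief and average pain intensity during the past week (NRS"). The 12-week visit and the visit 12 weeks after treatment list questionnaires, stimulation tests and blood sampling, but no expectation or desire rating.
- **Numerical Rating Scale.** The expectation item reads "What level of pain do you expect when this treatment starts to have an effect", on a scale "anchored at the left by the descriptors ‘no pain sensation’ and at the right by ‘the most intense pain sensation imaginable". The section calls the result a rating of expected pain level and repeats that it is taken before each injection, on the scale used for pain.
- **Statistical methods.** Ratings of desired and "expected treatment outcome pretreatment and post treatment will be implemented in linear regression models to predict any of the outcome measures". A second set of regressions uses each participant's SD over the repeated ratings as predictor. No covariates are named, and none are ruled out.

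**The concern.** **Timing of the predictor.** With 12 weekly injections and a rating before each, only the first rating is truly pretreatment. The last is made after up to 11 injections. No visit after the last injection schedules such a rating, so the post-treatment rating in Statistical methods is either a late on-treatment rating or one without a scheduled occasion. On either reading the woman may already know whether her pain has changed. Her rating can then be partly a consequence of the response that it is meant to predict. The SD of repeated ratings has the same weakness, because steady improvement over 12 weeks raises it.

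**Content of the item.** The objective is named as expected effect, but the item records an expected level, that is, current pain minus expected relief. A woman at 6 who hopes for 1 point of relief and a woman at 9 who hopes for 4 both answer 5. The score therefore contains current severity, which may be related to the outcome for reasons unrelated to expectation.

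The article lists placebo effects of injection among its possible limitations, and these regressions are where it examines expectation. An association produced by severity or by felt response could be reported there as an effect of expectation.

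**Working it through.** The documents give no figure for these regressions, so there is none to reproduce. From the documents come the total of 40 participants (Sample size), the rating before each of 12 weekly injections, and the item wording. Everything else is an assumption. The test is two-sided at 5%, and expectation has no true effect in any setting.

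**1. Expected level as predictor, pretreatment rating**

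Assumed: current pain P with SD 2; expected relief R = s·P + e, with SD(e) = 1.5; expected level L = P − R; outcome Y with correlation ρ to P and no other link to L. The slope s says how far women in more pain expect more relief. Values 0, 0.5 and 0.7 were tried.

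- corr(L, P) = 2(1 − s) / √[4(1 − s)² + 1.5²]
  - s = 0: 2/2.5 = 0.80
  - s = 0.5: 1/√3.25 = 0.555
  - s = 0.7: 0.6/√2.61 = 0.371
- corr(L, Y) = ρ × corr(L, P)
- Rejection rate ≈ Φ(√37 × atanh[corr(L, Y)] − 1.96), with 37 = 40 − 3

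Example, s = 0 and ρ = 0.5: corr(L, Y) = 0.40; √37 × 0.4236 = 2.58; Φ(0.62) = 73%.

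Simulation of the same model (10,000 samples of 40 per setting) gave:

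| s | ρ | L alone | Relief score R alone | L with P as covariate |
|---|---|---|---|---|
| any | 0 | 5% | 5–6% | 5% |
| 0 | 0.3 | 32% | 5% | 5% |
| 0 | 0.5 | 74% | 5% | 5% |
| 0.5 | 0.3 | 18% | 18% | 5% |
| 0.5 | 0.5 | 41% | 42% | 5% |
| 0.7 | 0.3 | 11% | 25% | 5% |
| 0.7 | 0.5 | 21% | 59% | 5% |

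The difference score (past-week pain minus expected pain) holds its level only when s = 0 or ρ = 0. At s = 0.7 it does worse than the raw level. Only the model with current pain as covariate stays near 5% in every row.

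**2. Late rating as predictor, adjusted for baseline pain**

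Assumed: response D with SD 1.5; outcome = baseline pain − D + noise of SD 1; late rating = baseline pain − k·D − further expected relief (SD 1.5, unrelated to outcome). Here k is the share of the response already felt when the rating is made.

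- Given baseline pain, the partial correlation is 2.25k / √[3.25 × 2.25(1 + k²)]
  - k = 0.25: 0.202
  - k = 0.5: 0.372
  - k = 1: 0.588
- Rejection rate ≈ Φ(√36 × atanh[r] − 1.96), with 36 = 40 − 1 − 3: 23%, 65% and 98%

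Simulation with ratings rounded and bounded to 0–10 gave 22%, 64% and 98%. The pretreatment rating in the same model gave 5%. Adjustment for baseline pain therefore does not repair a late rating.

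**The case against.** - **Covariates may be specified elsewhere.** This is a condensed article, and an analysis plan may name them. That stands: the article's silence is not in itself an error, and the figures in step 1 apply only if current pain is left out. It does not answer step 2, because the use of post-treatment ratings as predictors is stated outright and baseline adjustment does not cure it.
- **The scales are described as validated and used before, and the item is openly called an expected pain level.** Also fair. Nothing here shows the item to be invalid. But validation of a rating does not turn a level into an expected change, or a rating made after response into a predictor of it.
- **The false-positive rate depends on assumptions.** It does. A reader might infer that the trial will report a spurious expectation effect. The documents do not support that: at correlation 0 the error stays at 5%, and if women in more pain expect more relief the rate falls well below the independence figures. The correlation is likely for pain NRS, MPQ and the RAND-36 pain items. For cold-pressor tolerance the document gives no basis for it.
- **A late rating still precedes the outcomes 12 weeks after treatment ends.** True in time, so it does not simply follow from those outcomes. Response felt by then can still drive both.
- **These analyses are secondary.** Agreed. A reader might also infer that the mecobalamin–placebo comparison is weakened. It is not, since these ratings play no part in it.

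**Conclusion.** The point holds in two parts of unequal weight.

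The firmer part rests on what the article states. Ratings taken after treatment has begun are to predict outcome, and no rating after the last injection is scheduled. Such an association cannot be read as an effect of expectation. With baseline pain in the model, false positives were 22%, 64% and 98% when the late rating carried 25%, 50% or 100% of the response felt, under the assumed SDs.

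The second part is conditional. Because the item is an expected level, a regression that omits current pain can show a false expectation effect for outcomes correlated with current pain. With pain SD 2 and relief SD 1.5, the rate is about 32% at correlation 0.3 and 74% at 0.5 if relief is independent of pain. If relief rises with pain, it is about 10–42% over the same correlations. It is 5% at correlation 0, and about 5% throughout once current pain is a covariate.

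Both parts concern secondary analyses only.

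**What to change.** In Statistical methods:

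1. Use as predictors the expectation and desire ratings made before the first injection. Include the average past-week pain rated on that occasion and treatment group as covariates. An unadjusted difference between current and expected pain is not a sufficient substitute.
2. Do not use post-treatment ratings as predictors of effect. Report them, and the SDs of repeated ratings, as descriptive associations, and state which scheduled rating is meant.

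No new data are needed, because past-week pain is already rated before each injection. The cost is one or two degrees of freedom, and the regressions on late ratings and on SDs lose their predictive reading.
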